**1. Problem Statement****1.1 Stress Urinary Incontinence (SUI)**

SUI is defined as any involuntary loss of urine resulting from physical exertion such as jumping, running, sneezing, or coughing. SUI seriously impairs women's quality of life, affecting social, emotional, and economic aspects. The prevalence of this dysfunction in women varies from 12% to 55%.

It is believed that SUI is caused by a combination of risk factors, with the most important being the number of pregnancies and the mode of delivery. Vaginal delivery can cause damage to the support and suspension structures of the pelvic floor and urethra, such as the vaginal mucosa, muscles, endopelvic fascia, and ligaments. These structures are mainly composed of smooth and striated muscles, and connective tissue. Some studies describe biochemical and molecular alterations in the tissues of women with SUI compared to continent women, such as a significant reduction in the amount of type I and III collagen around the urethra and in the pubocervical fascia; a decrease in the ratio of striated muscle to connective tissue, as well as histological reduction of striated muscle fibers; and partial nerve lesions in the urethral striated sphincter. Thus, it is believed that damage to the components of the urethra, with consequent

reduction of intra-urethral pressure, is associated with the pathophysiology of urinary incontinence.

Regenerative medicine is a new area of medicine that incorporates various fields of tissue engineering. Among these, the use of stem cells stands out for the development of biological substitutes to restore and maintain the original functions of organs and tissues. As an alternative to surgical treatment, cell therapy using stem cells has been considered promising for the management of SUI due to its potential ability to restore the urethral sphincter.

## **1.2 Adult Stem Cells (ASCs)**

Stem cells (SCs) are undifferentiated cells with the potential to differentiate into specialized cells that are more complex both structurally and functionally when stimulated by an appropriate tissue microenvironment. They serve as sources for repair of tissues and organs in a virtually unlimited way throughout life. They can be of embryonic origin (ESCs), adult origin (ASCs), or induced pluripotent stem cells (iPSCs).

Adult stem cells (ASCs) are found in fully developed tissues or organs: bone marrow, peripheral blood, brain, spinal cord, dental pulp, blood vessels, skin and digestive tract epithelia, cornea, retina, liver, pancreas, and skeletal muscle. Their main functions in a living organism are to maintain tissue homeostasis, that is, to renew it whenever necessary and to replace cells damaged by trauma or disease. This distinguishes them from embryonic stem cells (ESCs), since ASCs seem to differentiate only into more specific cell types restricted to the tissues they belong to. However, some types of ASCs have greater plasticity, meaning the cells can differentiate into cell types that do not share the same embryonic origin.

ASCs involve less complex manipulation and greater safety in therapeutic applications, since there is a very low chance of these cells causing tumors compared to ESCs.

Experimental and clinical research has been conducted to evaluate the viability, safety, and effects of using ASCs in the repair of damaged urethral tissues. Among the ASCs, the most commonly used and studied in urogynecology are muscle-derived stem cells (MDSCs), adipocyte-derived stem cells (ADSCs), and bone marrow-derived stem cells (BMSCs).

## **1.3 Use of Muscle-Derived Stem Cells in Urethral Regeneration**

Muscle-derived stem cells (MDSCs) mainly differentiate into mesodermal cells (striated muscle, fat, cartilage, and bone). They are obtained by purifying samples of striated muscle and cultured in vitro. The cultured cells can then be injected directly into the area to be treated (damaged tissue) or into the bloodstream, depending on the type of regeneration intended.

Chermansky et al. demonstrated that after periurethral injection, MDSCs integrated into the striated sphincter muscle layers of rat urethras four weeks after urethral injury by cauterization. Moreover, there was regeneration of innervation in the group injected with MDSCs compared to the placebo group that received saline solution, suggesting the multipotency of MDSCs. In the same study, the leak point pressure (intravesical pressure at which urinary leakage occurs during the Valsalva maneuver) was significantly higher in the MDSC group compared to the control group, indicating better urethral function in the treated group. There was no significant difference in leak point pressure in the treated group after 4 and 6 weeks post-injury compared to the uninjured group, suggesting that the urethral function ensuring urinary continence in the group that received MDSCs was similar to that of normal rats, and thus restored.

A recent study demonstrated the beneficial effects of cell therapy with MDSCs in monkeys with stress urinary incontinence caused by transection of the pudendal nerves. The authors performed histological analyses and functional urodynamic studies to evaluate the therapy after one year. They observed that the therapy increased the maximum urethral closure pressure in the monkeys, showed a higher proportion of striated muscle area, and a smaller collagen fiber area in the urethras of treated animals compared to untreated controls. Three months after injection, muscle markers (desmin, connexin-43, and  $\alpha$ -smooth muscle actin) and Von Willebrand factor were detected, marked with GFP fluorescent protein from the stem cells. Thus, differentiation of MDSCs into muscle tissue and blood vessels was confirmed. The study demonstrates the long-term beneficial outcomes of MDSC therapy for stress urinary incontinence.

Carr and colleagues recently published a clinical study involving 38 women with stress urinary incontinence refractory to one year of conventional clinical treatment. In phase 1, participants were randomized into five groups of 4, according to the number of cells they received: 1, 2, 4, 8, and 16 million MDSCs. In phase 2, three groups of 3 participants received 32, 64, and 128 million cells, and in phase 3, another three groups of 3 participants received 16, 32, and 64 million cells injected periurethrally via cystoscopy. Patients could opt for a second injection after 3 months. Evaluation was performed through periodic analysis of voiding diaries, pad tests, and quality of life questionnaires during 12 months of follow-up. Therapy outcomes improved proportionally to the number of cells used. Compared to low-dose groups, a higher proportion of participants in the high-dose groups showed at least a 50% reduction in pad weight during the pad test (88.9%, 8 of 9 vs. 61.5%, 8 of 13), at least a 50% reduction in stress urinary leakage recorded in voiding diaries (77.8%, 7 of 9 vs. 53.3%, 8 of 15), and had up to one leakage episode over 3 days (88.9%, 8 of 9 vs. 33.3%, 5 of 15) at the final one-year follow-up. The reported side effects were few: pain at the muscle biopsy site and injection site, mild and temporary urinary retention, and urinary tract infections.

Consistent results regarding the safety and efficacy of cell therapy with local periurethral injections of MDSCs for the treatment of female stress urinary incontinence were observed by Peters and collaborators (2014). Using a similar methodology, the authors evaluated 80 women who received injections into the external urethral sphincter of 10 (n=16), 50 (n=16), 100 (n=24), or 200 (n=24) million autologous MDSCs obtained from quadriceps muscle biopsies. All groups had statistically significant improvement in scores of specific questionnaires evaluating urinary incontinence (UDI-6 and IIQ-7) at 6 and 12 months of follow-up compared to pre-treatment status. Overall, clinical improvements were dose-dependent. Eighty-five percent of patients who received 100 million cells and 77% who received 200 million stem cells showed at least a 50% reduction in stress-related urinary leakage according to voiding diary analysis, an instrument that differentiates types of urinary incontinence. Both doses improved pad test values, with significance reached in the 200 million cell group. However, the authors highlighted that about 50% of patients evaluated had mixed urinary incontinence. Thus, pad test values would not differentiate stress or urgency-related leakage, raising questions about conclusions based solely on the pad test. The authors did not observe serious or persistent adverse effects with therapy at any dose administered.

A single randomized study compared autologous MDSC urethral injection with three different surgical techniques for correcting stress urinary incontinence ("Burch, TVT sling, and TOT sling"). The study involved 8 women who received cell therapy, 11 in the Burch group, 26 TVT sling cases, and 41 TOT sling cases. The authors reported slight but not significant improvement in functional parameters in the urodynamic study after MDSC therapy. The results were inferior to those

obtained with surgical procedures, indicating the need for a larger sample size to draw conclusions about the effects of cell therapy.

#### **1.4 The Use of Adipose-Derived Stem Cells in Urethral Regeneration**

Adipose-derived stem cells (ADSCs) are obtained from white adipose tissue (the most predominant in adults), which is composed of 40-60% mature adipocytes and a stromal fraction, this fraction consisting of fibroblasts, macrophages, mast cells, endothelial cells, hematopoietic cells, and pre-adipocytes. Pre-adipocytes are the precursors known as ADSCs. It has been demonstrated that these cells can differentiate in vitro into adipogenic, myogenic, and osteogenic cells. They may have a role in the treatment of urinary incontinence. Jack et al. demonstrated smooth muscle formation from ADSCs in the detrusor muscle, with contractile and relaxation capacity; meanwhile, Zeng et al. achieved positive results in animal models with rats, improving leak point pressure (LPP) and urethral function after injection of ADSCs into injured urethras.

In clinical practice, there is a report of two cases of patients who received ADSC injections after radical prostatectomy. These patients had moderate stress urinary incontinence (SUI) after surgery for at least 2 years, were not undergoing treatment for SUI, and had no disease recurrence. About 250 ml of adipose tissue was harvested from the anterior abdominal wall, and ADSCs were subsequently isolated. Then, the cells were injected into the paraurethral tissue in the external urethral sphincter region via cystoscopy. One milliliter of pure ADSC solution was applied to the rhabdosphincter (at a depth of 5 mm), and 20 ml of a solution containing intact adipose tissue and ADSCs was injected into the submucosa as a sealing agent. The results were encouraging: progressive improvement of SUI (measured by 24-hour pad test and questionnaire), increased functional urethral length, and increased mean urethral closure pressure. Ultrasound showed that the material injected into the paraurethral region did not disappear after 12 weeks, and Doppler imaging detected blood flow in the area where ADSCs were applied. No side effects were reported.

#### **1.5 The Use of Bone Marrow-Derived Stem Cells in Urethral Regeneration**

Bone marrow is a very important source of stem cells. The mesenchymal lineage (mesenchymal stem cells - MSCs) is the most relevant in this field, as it can develop into bone, cartilage, fat, and connective tissue. Most studies with these cells have focused on bladder regeneration in animal models, using acellular matrices seeded with MSCs. The cells were cultured in vitro and seeded onto acellular matrices (intestinal submucosa), which were implanted into the animals' bladders, resulting in the development of functional smooth muscle from the MSCs.

In addition, there is a study by Kinebuchi et al. that analyzed urethral sphincter regeneration in rats. Seven days after surgically induced injury, the rats were re-operated and received injections of 200,000 to 500,000 MSCs suspended in culture medium into the periurethral tissue. These were compared with animals injected only with culture medium and with animals without urethral injury. Leak point pressure (LPP) values were evaluated for each group before injury and at 1, 4, 6, 8, and 12 weeks after injection (cells or pure culture medium). Rats without injury showed no difference in LPP measurements. Injured rats treated with injections of only culture medium had significantly reduced LPP after 1 week and did not recover up to the 12th week. Rats treated with MSCs showed gradual recovery of LPP, but this was not significantly greater than in the culture medium-only group. Histologically, skeletal muscle proliferation was observed in the

MSC group, but no smooth muscle proliferation. Additionally, increased innervation was observed in the MSC group.

#### **1.4 UNIFESP-EPM Experience**

The Urogynecology and Vaginal Surgery Sector of the Department of Gynecology at UNIFESP-EPM has an ongoing research line focused on stem cell therapy (SCT). This research project initially received support from the National Council for Scientific and Technological Development (CNPq): CT-Health/MS/SCTIE/Decit/MCT/CNPq Call No. 17/2008.

We analyzed the effect of administering muscle-derived, adipocyte-derived, and bone marrow-derived stem cells in an animal model of urethral trauma induced by vaginal distension (VD), which mimics urethral injuries resulting from vaginal delivery. We studied and compared the urethras of three groups of rats: control, VD group, and VD group treated with stem cells. The VD technique was developed and standardized in our laboratory, in which a Foley catheter was inserted into the vagina of rats with the balloon maintained inflated with 3 ml of water for intermittent periods of 12 hours. Urethral injuries were confirmed by histological analyses.

Stem cells were obtained from mutated SD-Tg(GFP)2BalRrrrc rats that express the “green fluorescent protein” (GFP) marker in their cells, which are easily detected due to the green color they reflect under fluorescent light (Figure 1).

The cells were cultured and expanded in an appropriate medium. We confirmed the authenticity of the MSCs through a combination of cell differentiation assays, immunophenotyping, and cell cycle phase determination. MSCs, for example, differentiated in vitro into adipocytes, chondroblasts, and osteoblasts, characterizing their potential to mature into cells of the three germ layers (Figure 2).

After completing the cell culture phase, we treated the rats 72 hours after VD injury by injecting the GFP-labeled stem cells into the animals' tail vein. Subsequently, identification of GFP-labeled cells and tissue morphology of the urethra were evaluated on days 7, 14, 21, and 28 post-therapy using histochemical analysis and electron microscopy

We observed that the rats subjected to trauma by vaginal distension (VD) showed disorganization in the histological layers of the urethra, characterized by narrowing and rupture of the smooth and striated muscle fibers.

At 28 days post-trauma, we observed the presence of connective tissue partially replacing the smooth muscle fibers, suggesting a scarring process (Figure 3).

We observed the early presence (7 days after injection) of GFP-labeled cells in all layers of the urethra, demonstrating their migration, integration, and survival within the urethral tissue. Cell therapy improved the structural organization of the urethras and tissue remodeling compared to untreated traumatized rats. After 4 weeks of treatment, we observed equal proportions of smooth muscle and connective tissue in the urethra, as well as extensive recovery of striated muscle, both similar to the structural pattern of control rats (Figure 3).

Our results with the use of bone marrow-derived stem cells (BMSC), muscle-derived stem cells (MDSC), and adipose-derived stem cells (ADSC), and their effects on the urethra were very similar.

Immunohistochemical analyses using desmin marker (a marker of smooth and striated muscle) demonstrated improved structural organization and thickness of the urethral muscle layers in

rats treated with MDSC compared to untreated rats after trauma (Figure 4). These findings suggest the beneficial effect of MDSC therapy on urethral regeneration.

In order to understand the effects of cell therapy with muscle-derived stem cells (MDSC) at the molecular level and associate them with histological findings, we performed gene and protein expression studies of the urethras from rats. We compared the control group without DV trauma, the DV group without cell therapy 28 days after trauma, and the group that underwent DV and was treated with MDSC. Markers of smooth and striated muscle, cell proliferation markers, and growth factors were studied.

Regarding gene expression, we observed an increase in the cell proliferation gene Ki67 and collagen genes 1 and 3 in the group treated with MDSC; meanwhile, the heavy chain genes of smooth and striated muscle, as well as the neural growth factor NGF, were elevated in the trauma groups and practically returned to baseline levels after treatment. The vascular growth factor VEGF did not show alteration at different time points (Figure 5).

We focused our protein analysis on muscle components: heavy chain myosins of smooth muscle (MHY11) and striated muscle (MHY1), and observed a significant increase in protein expression in the groups of rats that received therapy with MDSC, demonstrating the regenerative effects of the urethral therapy (Figure 6).

In addition, this study demonstrates the safety of therapies with adult stem cells (ASCs). We did not observe any cases of rejection, tumor formation, or other complications in our trials.

Note: see Figures in the original version of the protocol.

## **2. Expected Results**

Given the experimental findings that suggest significant recovery of urethral components and structure, cell therapy with ASCs could be viable and useful for treating women with stress urinary incontinence (SUI), as it would aid the regeneration process of damaged urethras, such as those injured by vaginal birth trauma.

However, the effects of cell therapy in clinical practice have not yet been sufficiently demonstrated, and additional clinical studies are needed to confirm its viability and potential benefits for incontinent women. Therefore, we are interested in continuing research in this field.

We expect to demonstrate that therapy with ASCs derived from skeletal muscle (MDSCs), bone marrow (BMSCs), and adipocytes (ADSCs) is viable for treating SUI and improves quality of life and urinary leakage in affected women.

## **3. Scientific and Technological Challenges**

### **3.1 General Objective:**

The objective of this study is to evaluate the viability and effects of urethral injection therapy with bone marrow-derived stem cells (BMSCs), muscle-derived stem cells (MDSCs), and adipose-derived stem cells (ADSCs) in women with stress urinary incontinence (SUI).

### **3.2 Specific Objectives:**

- Isolation and in vitro cultivation of autologous MDSCs, BMSCs, and ADSCs obtained from urogynecological patients with SUI;

- Analysis of the viability of intra-urethral cell therapy in women with SUI regarding methodology and potential adverse effects;
- Evaluation of women after cell therapy using objective parameters to assess urinary leakage: stress test, pad test, and urethral closure pressure assessment by urodynamic study;
- Evaluation of women after cell therapy using subjective parameters through the application of a quality of life questionnaire specific for urinary incontinence (I-QOL).

## **4. Methodology**

### **4.1 Study Design and Population:**

Prospective randomized clinical study involving 45 patients with SUI who will receive peri-urethral injection of 5 ml solution containing 100 million autologous ASCs (derived from muscle, bone marrow, or adipose tissue).

### **4.2 Study Location:**

This is a joint study between the Urogynecology Sector, General Gynecology Discipline, Department of Gynecology at the Federal University of São Paulo (UNIFESP), and the Hematology and Hemotherapy Sector of the Hospital Israelita Albert Einstein Hospital (HIAE), São Paulo, SP, and the private company Stemcorp, São Paulo, SP.

### **4.3 Participants**

#### **Inclusion Criteria**

1. Patients with moderate stress urinary incontinence (SUI), primary and refractory to previous clinical treatments (behavioral therapy and physiotherapy), confirmed by physical examination (stress test), I-QOL questionnaire, cystometry (urodynamic study), and pad test (between 10 and 50 grams).

#### **Exclusion Criteria**

1. Patients with anterior vaginal wall or uterine prolapse greater than stage 2 (POP-Q classification);
2. Patients previously submitted to surgical procedures for SUI correction;
3. Patients with genital malformations that prevent injection in the mid-urethral site;
4. Patients with previous pelvic radiotherapy;
5. Patients who during clinical and/or urodynamic evaluation present other diagnoses besides SUI (mixed incontinence, urge incontinence, detrusor overactivity, paradoxical incontinence, neurogenic bladder, urinary obstruction);
6. Patients who do not consent to participate in any stage of the study or who are unable to read, write, and understand the study;
7. Patients under 18 years of age.

### **4.4 Location of Procedures**

Patients will be recruited and evaluated (pre- and post-treatment) at the Urogynecology Outpatient Clinic of UNIFESP. Procedures for bone marrow biopsy, cell isolation, and cultivation will be performed at the human cell therapy laboratory in the Hematology and Hemotherapy Sector of Hospital Israelita Albert Einstein, São Paulo. Procedures for adipose tissue and biceps muscle biopsy will be performed in the surgical center of the Hospital São Paulo, and the cell isolation and culture procedures will be carried out at the Stemcorp Cell Therapy Laboratory, São Paulo.

#### **4.5 Pre- and Post-Therapy Diagnostic Tests**

##### **a) Clinical Examination – Stress Test:**

To diagnose urinary incontinence, a stress test will be performed in which urine leakage is evidenced when the patient performs strain maneuvers with a comfortably full bladder.

##### **b) Pad Test:**

The pad test will be used to quantify urine loss. With an empty bladder, 250 ml of distilled water will be instilled into the bladder. A pre-weighed pad will then be placed in the perineal region, and the patient will perform the following stress maneuvers: coughing, jumping, squatting, and abdominal muscle contraction (Valsalva), ten times each. Additionally, they will climb five steps ten consecutive times, wash their hands for one minute, and walk for twenty minutes. The total test duration will not exceed one hour. Afterwards, the pad will be weighed; a weight difference greater than 2 grams will be considered a positive test. [34]

##### **c) Cystometry:**

The urodynamic test will be conducted using the Urosystem PL-2400 Polimed four-channel device. Cystometry will be performed with the patient in a semi-seated position using a two-way urethral catheter—one channel for bladder filling and the other for intravesical pressure measurement. Room-temperature distilled water will be infused at a rate of 40 ml/min. Abdominal pressure will be monitored using a rectal balloon. During the filling phase, when 200 ml have been infused, the patient will perform a Valsalva maneuver to determine the intravesical pressure at the moment of urinary leakage through the urethra. The test will be considered positive whenever urine leakage occurs, and the leak point pressure (LPP) will be recorded.

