#### **5. Post-Procedure Evaluation**

The patient will be observed for two hours following the procedure. Follow-up visits will occur at 7, 30, 60, and 180 days for clinical evaluation after treatment.

One year after the procedure, patients will complete another round of questionnaires, pad test, and cystometry with leak point pressure evaluation. These data will be disclosed only after the final assessment of the entire study population.

The **primary outcome** is improvement in quality of life, which will be assessed using the I-QoL questionnaire before and after treatment. Patients scoring between 0 (complete cure) and 20 (inclusive) on the post-treatment I-QoL will be considered improved. Patients with scores above 20 will be considered not improved.

In addition, patients will be considered cured if they show no signs of urinary leakage during the clinical examination, cystometry, or pad test.

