## 6. Statistical Method

**Data processing and analysis:** The SAS software version 8.2 will be used to verify data consistency and perform statistical analysis.

**Descriptive analysis:** Descriptive analysis will be used to characterize the study sample. For categorical variables, absolute and relative frequency distributions will be used. For continuous variables, measures of central tendency (mean and median) and variability (standard deviation, upper and lower limits) will be applied.

**Inferential analysis:** Comparisons between pre- and post-treatment parameters will be analyzed using the *Wilcoxon rank-sum test* and *Student's t-test* for non-parametric and parametric variables, respectively. The *Chi-square test* and *Fisher's exact test* will be used to assess the homogeneity of categorical variables (race, hormonal status, and previous surgeries for stress urinary incontinence), as well as the absence of urinary leakage on urodynamic testing after the intervention. The *Mann-Whitney test* will be applied to assess the homogeneity and possible differences in medians of continuous variables between pre- and post-treatment groups that measure treatment success measured by the "I-QoL" questionnaire and pad test) will be assessed. For all statistical tests, a significance level of 0.05 or 5% ( $\alpha \leq 0.05$ ) will be adopted as the threshold for rejecting the null hypothesis.

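### A one-year cystometry counts as dry at any strain effort, so a woman with an unchanged urethra can be scored dry on the urodynamic outcome and pass the cystometry component of cure.

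*Protocol*

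**What the plan says.** Section 4.5 c) describes one manoeuvre: "when 200 ml have been infused, the patient will perform a Valsalva maneuver to determine the intravesical pressure" at which leakage occurs. The scoring rule is "The test will be considered positive whenever urine leakage occurs, and the leak point pressure (LPP) will be recorded". A test without leakage is by implication negative. The section gives no minimum or target strain, no repeat and no category for an inadequate strain. Effort is measured, since "Abdominal pressure will be monitored using a rectal balloon" and the catheter gives intravesical pressure, but no rule uses either reading to qualify a dry test. The only value named for recording is the LPP, which a dry test does not yield.

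At entry (section 4.3) stress incontinence must be "confirmed by physical examination (stress test), I-QOL questionnaire, cystometry (urodynamic study), and pad test (between 10 and 50 grams". At follow-up (section 5), "One year after the procedure, patients will complete another round of questionnaires, pad test, and cystometry with leak point pressure evaluation".

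A dry cystometry is used in two places:
- Section 6 assigns chi-square and Fisher tests to baseline categorical variables "as well as the absence of urinary leakage on urodynamic testing after the intervention".
- Section 5 states that "patients will be considered cured if they show no signs of urinary leakage during the clinical examination, cystometry, or pad test".

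The primary outcome in section 5 is the I-QoL. Section 6 names the I-QoL and the pad test as the measures of treatment success.

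**The concern.** Section 1.3 of the protocol explains LPP as the intravesical pressure at which urine leaks during a Valsalva. A strain below that pressure produces no leak whether or not the urethra has improved. A dry test at a lower pressure than the one at which she leaked at entry is therefore uninformative, yet it is scored like a dry test at full effort.

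The error has a direction. If women enter because they leaked on cystometry, they were selected on an occasion when their strain was sufficient. In a woman who has not changed, variation in effort at one year can then move the result only from wet to dry. All 45 women receive cells (section 4.1), so no untreated group shows how large that drift is.

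At stake is the one binary continence result that section 6 names for testing, and one component of cure. If the peak pressure of a dry test is not kept, no later analysis can separate a weak strain from a real change.

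**Working it through.** The protocol gives no power calculation and no LPP or strain distribution, so there is no stated figure to reproduce. Everything in steps 1 and 4 rests on assumed inputs and shows scale only.

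**1. False-dry rate with no true change**

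Let L be a woman's LPP, the same at entry and at one year. Let S1 and S2 be her peak strain on the two occasions, each equal to her own mean strain plus occasion error. She enters if S1 ≥ L and is falsely dry if S2 < L, so q = P(S2 < L | S1 ≥ L).

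Assumptions: L normal with mean 60 or 80 cmH2O and SD 20; a woman's mean strain normal with mean 110 and SD 20; occasion SD 10, 15 or 20. Evaluated by simulation:

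| Mean LPP | Occasion SD | q | Expected of 45 (45 × q) | P(at least 6 of 45) |
|---|---|---|---|---|
| 60 | 10 | 1.9% | 0.9 | 0.0002 |
| 60 | 15 | 3.2% | 1.4 | 0.003 |
| 60 | 20 | 4.8% | 2.2 | 0.02 |
| 80 | 10 | 5.4% | 2.4 | 0.03 |
| 80 | 15 | 8.3% | 3.7 | 0.16 |
| 80 | 20 | 11.1% | 5.0 | 0.39 |

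The last column is the binomial tail 1 − Σ C(45, x) q^x (1 − q)^(45 − x) for x = 0 to 5.

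**2. How many false-dry results would matter on a pre/post reading**

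Assume 45 of 45 leaked at entry and k of 45 are dry at one year. The two-sided Fisher p is 2 × C(45, k) / C(90, k).
- k = 6: 2 × 8,145,060 / 622,614,630 = 0.026
- k = 5: 2 × 1,221,759 / 43,949,268 = 0.056

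The same women are measured twice, so the paired check is exact McNemar, 2 × 0.5^k: 0.031 for k = 6 and 0.063 for k = 5. Both tests put the threshold at 6 of 45 (13%).

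**3. On a between-arm reading**

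If section 6 instead compares the three cell sources after treatment, effort variation common to the arms raises the dry rate in all of them. It adds noise and does not create a false difference.

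**4. Effect on cure**

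Read as dry on all three tests, cure also needs a dry stress test and a pad gain of no more than 2 g (section 4.5 b). Assume each of these is falsely dry with probability m = 0.05 to 0.20, and take a deliberately wide q = 0.10 to 0.30. If the tests err independently, the false-cure rate is q × m²:
- lowest: 0.10 × 0.05² = 0.03%, about 0.01 of 45
- highest: 0.30 × 0.20² = 1.2%, about 0.5 of 45

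If all three tests fail in the same women, the upper bound is the smallest of the three rates, 5% to 20%, or about 2 to 9 of 45.

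**The case against.** A reader might infer that a weak strain turns an unchanged woman into a treatment success. The protocol does not support that. The I-QoL does not use cystometry, and cure on its natural reading requires all three tests to be dry. She entered with a pad gain of 10 to 50 g, and the pad test repeats coughs, jumps, squats and Valsalvas ten times each at 250 ml, with stairs and a walk. One soft strain at cystometry does not make that test negative. The stronger claim would hold only if the word or in the cure sentence meant that one dry test is enough, which is not how it naturally reads. This objection stands and limits the point to the urodynamic outcome and one component of cure.

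Three further objections stand in part.
- Section 6 does not say whether the chi-square/Fisher comparison is pre/post or between arms. The p values in step 2 hold only on the first reading.
- Leakage at the entry Valsalva is inferred from the requirement that incontinence be confirmed by cystometry. It is not stated, so a recorded entry LPP for every woman cannot be taken for granted.
- With unchanged effort, the expected number of false-dry results stays below 6 in every setting, and the chance of 6 or more is below 4% in four of the six. If mean strain is assumed 10% weaker at one year, q becomes 5.1% to 19.3% (2.3 to 8.7 of 45). It is tempting to suppose that women strain more cautiously after a urethral injection, but nothing in the protocol says so, and the point does not rely on it.

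It may also be said that strain adequacy can be judged from the pressure traces. It could be, but no rule asks anyone to do so, and only the LPP is named for recording.

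**Conclusion.** The point holds in limited form. Section 4.5 c) lets a cystometry be negative at any strain effort, so an unchanged woman who strains below her entry LPP is scored dry on the section 6 urodynamic outcome and passes the cystometry component of cure. The primary outcome is untouched, and cure as a whole is largely protected by the other two tests unless all three fail in the same women.

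On the assumed inputs, with no change in effort, the size is about 2% to 11% falsely dry, or roughly 1 to 5 of 45. That is usually too few to give a significant result alone, but it would inflate the reported dry rate. A false significant result also needs the pre/post reading, leakage in all 45 at entry and 6 or more false-dry tests. This is a cheap improvement to the scoring of a secondary outcome and no threat to the trial's main conclusion.

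**What to change.** In section 4.5 c):
1. Record the peak intravesical and abdominal pressure at every Valsalva, whether or not she leaks.
2. Score a post-treatment cystometry as negative only if there is no leak and the peak intravesical pressure reached at least the woman's own pre-treatment LPP, where one was recorded.
3. If that pressure is not reached, repeat the manoeuvre within the same filling.
4. If it is still not reached, or no entry LPP exists, class the test as not assessable. Do not count it as dry in section 6 or in the cure rule, and report how many such tests there were.

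In section 6, state whether absence of leakage is compared with entry or between the three arms.

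Cost: one scoring rule and the peak pressures, from sensors already in place. The downside is possibly a few extra strains in the same test and a slightly lower reported dry rate. The rule removes variation in effort; it does not remove measurement error in the LPP itself.
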